### Measures

The primary outcome measures assess everyday PM performance and level of psychosocial reintegration. Secondary outcome measures assess PM performance and strategy use, global self-awareness, self-awareness of PM failure, and level of support needs. Primary and secondary outcome measures will be administered at pre and post intervention, and at 3-month and 6-month follow-ups.

#### Primary outcomes

The Brief Assessment of Prospective Memory (BAPM; [38]) is a 16-item self-report scale which measures frequency of PM failure in everyday life over the past month. The BAPM consists of two subscales: basic activities of daily living (eight items) and instrumental activities of daily living (eight items). Subscale scores range from 0 to 5, with higher scores reflecting more frequent PM failure. Internal consistency and test-retest reliability have been reported [37]. Significant other ratings will be used in this study, rather than self-ratings, in order to overcome confounding scores due to the development of self-awareness in TBI participants over the course of the intervention.

The Sydney Psychosocial Reintegration Scale version 2 (SPRS-2; [39, 40]) is a 12-item questionnaire which assesses an individual’s level of psychosocial reintegration following TBI. The SPRS-2 contains two forms which reflect different comparison standards: Form A measures change since injury and Form B measures current status. Each form uses the same 12 items which measure three domains of functioning including occupational activities, independent living skills, and interpersonal relationships. Each domain contains four items, which are rated on a 5-point scale ranging from “no change” to “extreme change” (Form A) and “very good” to “extremely poor” (Form B). Scores range from 0–48, with higher scores indicative of better psychosocial functioning. The SPRS-2 (Form B) will be completed by participants’ significant others. Sound psychometric properties have been reported for the SPRS-2 [39].

#### Secondary outcomes

The Cambridge Prospective Memory Test (CAMPROMPT; [36]) is a psychometric test of PM function. The CAMPROMPT consists of a total of six PM tasks, three cued by time and three cued by events. Participants are allowed to spontaneously use strategies, such as taking notes, to help them remember during tasks. Total scores are out of 36 (time-based and event-based subscale scores are each out of 18), with higher scores representing better PM performance. The validity and reliability of the CAMPROMPT has been documented in a number of studies [36, 41]. In addition to total CAMPROMPT scores, participants’ spontaneous use of note-taking as a PM strategy during the CAMPROMPT will be measured as a dichotomous variable.

The Awareness Questionnaire (AQ; [42]) is a 17-item scale that assesses self-awareness of brain injury-related impairments across sensory, physical, cognitive, and behavioral domains. Ratings on the AQ compare participants’ post-injury abilities on each item to their preinjury functioning (1 = much worse, 5 = much better). The AQ has two versions, a self-report and a significant-other report which may be completed by a family member, friend, or therapist. Positive discrepancy scores (self-report minus significant-other report) indicate impaired self-awareness. The AQ has been found to have sound psychometric properties [43] and has demonstrated sensitivity to change in the context of awareness interventions [35].

Self-awareness specifically for PM impairment will be measured using the BAPM by calculating the discrepancy between participant self-ratings and significant other ratings of the frequency of PM failure in everyday life.

The Care and Needs Scale (CANS; [44]) is a clinician rating scale, designed to measure the types and level of support needs of a person with TBI. The types of support needs are assessed using a 24-item checklist, hierarchically grouped into categories reflecting the intensity of support required (such as support with special needs, basic activities of daily living, instrumental activities of daily living, and psychosocial supports). The information on types of support needs required by the individual is then used to evaluate the level of support needs, as indexed by the length of time that a person can be left alone. The CANS rating ranges from 0 (is completely independent) to 7 (cannot be left alone). Reliability of the CANS has been investigated by Soo et al. [45]. The CANS will be completed in conjunction with the participant’s referring occupational therapist.

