Three subtypes of PM have been identified in the scientific literature, according to task characteristics and the type of cue for recalling the intention [12]. These include: time-based PM activities when an action needs to be initiated at a particular time or window of time (e.g., in 10 min or before the close of business on Friday); event-based PM activities where an action is performed in response to an external cue (e.g., turn off the stove when the timer rings or ring a friend for their birthday when a reminder appears on your phone); and activity-based PM activities where an action is performed as part of or at the end of a sequence of actions or behaviors (e.g., put on your seatbelt after you get in the car or add sugar to your coffee after the milk). A study of the subtypes of PM using a computerized task showed that people with TBI performed significantly worse than controls on all subtypes [12]. In another study, patients with TBI had more difficulties compared to controls when the cognitive demand of the ongoing task was high, indicating their PM failures could be attributed to reduced processing capacity and problems allocating cognitive resources [4]. In previous research, significant others of patients with TBI reported that patients had significantly more instances of forgetting daily activities compared to non-injured controls [5]. In contrast, patients with TBI rated their own frequency of forgetting as similar to controls and reported fewer PM failures than their significant others, thus indicating a lack of self-awareness of their PM problems [5].

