### Study objectives and hypotheses

The primary aim of this RCT is to evaluate the effectiveness of a MST approach to compensatory PM training for improving everyday PM performance, maintaining PM gains, and improving level of psychosocial reintegration in community-dwelling adults with moderate to severe TBI. The secondary aim is to evaluate the effectiveness of a MST approach to compensatory PM training for improving and maintaining PM function on psychometric testing, strategy use, self-awareness, and level of care following TBI.

It is proposed that, with the addition of MST to the compensatory program, individuals with TBI will become aware of the extent of their PM failures, and the gains in PM performance will extend to everyday life as the participants will be able to generalize their strategy use to situations beyond the training setting. Therefore, it is hypothesized that:COMP training will demonstrate significant improvement at post intervention and maintenance at 3-months post intervention on PM performance and level of psychosocial integration compared to no intervention (i.e., waitlist), and that compensatory PM rehabilitation combined with metacognitive skills training (COMP-MST) will be more effective than COMP training aloneCompared to participants in the waitlist condition, participants who receive COMP training will demonstrate significant improvement and maintenance of PM function on psychometric testing, strategy use, self-awareness, and level of support needs and, furthermore, that COMP-MST training will be more effective than COMP training alone

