### Statistical analysis

Between-group differences will be calculated, accounting for baseline scores, for all three groups on all outcomes. To address the primary aim, unstructured linear mixed regression will be used to test for group differences on the primary outcomes, with group allocation (COMP-MST, COMP, waitlist control) as the between-subject factor, and time (baseline, post intervention, 3-month follow-up) as the within-subject or repeated variable. Any demographic or neuropsychological variables that are significantly associated with the primary outcome and unevenly distributed between the groups will be included as covariates. The same approach will be used with secondary outcome variables to address the secondary aim. Missing data will be handled using an intention-to-treat analysis (i.e., most recent available data will be imputed). Using planned comparisons, data from the 6-month follow-up will be compared with post-intervention and/or 3-month follow-up results to evaluate whether or not any significant gains on variables have been maintained over time.

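### The PM-awareness score contains the primary outcome as one of its two terms, so a memory gain can register, in whole or part, as an awareness gain

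*Protocol article*

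**What the plan says.** Under Primary outcomes, everyday PM is measured on the BAPM as rated by the significant other: "Significant other ratings will be used in this study, rather than self-ratings, in order to overcome confounding scores due to the development of self-awareness". On direction and range: "Subscale scores range from 0 to 5, with higher scores reflecting more frequent PM failure".

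Under Secondary outcomes, awareness of PM impairment is obtained by "calculating the discrepancy between participant self-ratings and significant other ratings of the frequency of PM failure in everyday life", using the same BAPM. A second awareness measure, the AQ, is a self-report minus significant-other score that covers sensory, physical, cognitive and behavioural domains.

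Under Statistical analysis, the primary outcomes go into a linear mixed regression with group and time. For the rest: "The same approach will be used with secondary outcome variables to address the secondary aim". No separate treatment of the two components of the gap is described.

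Two other statements bear on the point. In the Background, an earlier study is cited in which "patients with TBI rated their own frequency of forgetting as similar to controls and reported fewer PM failures than their significant others". The first hypothesis expects that "COMP training will demonstrate significant improvement at post intervention and maintenance at 3-months post intervention on PM performance", with COMP-MST better still; the second expects the same ordering for self-awareness.

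**The concern.** The significant-other rating is both a primary outcome and one of the two terms of the awareness score, so anything that moves the first also enters the second. The protocol sees one direction of this problem: it keeps self-ratings out of the primary outcome because growing awareness would distort them. It does not deal with the reverse, in which better memory lowers the significant-other rating and closes the gap without any change in insight.

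The trial's rationale is that MST raises awareness and that awareness carries strategy use into daily life. An awareness score that can move with the primary outcome is weak separate evidence for that account. The COMP versus waitlist comparison shows the risk most plainly. COMP contains no metacognitive training, yet a memory benefit alone could appear there as an awareness benefit.

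**Working it through.** The document gives no figure on this point, so there is none to reproduce.

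**Inputs from the protocol article**
- Primary outcome: significant-other BAPM (Primary outcomes).
- Awareness outcome: gap between self and significant-other BAPM (Secondary outcomes).
- Scale 0 to 5, higher is worse (Primary outcomes).
- Planned 30 per group with about 10% dropout (Sample size): 30 × 0.9 = 27 completers per arm.
- d = 0.70 (Sample size). This was derived for SPRS-2 change, so its use for the BAPM is an assumption.

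**Inputs not in the document (assumed)**
- Slope b of the self-rating on actual failures: 0 to 1.
- Equal SDs and zero correlation between the two ratings.

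**Algebra.** Let T be actual failures. Write significant-other rating = T + error and self-rating = a + b·T + error, and let awareness be represented by a and b, both held fixed. Then

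gap = significant-other − self = (1 − b)·T − a + error.

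If memory improves so that T falls by δ, the gap changes by −(1 − b)·δ. It is unchanged only when b = 1.

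**Check on the bounded scale.** This is a simulation with assumed baseline T of mean 2 and SD 0.8, error SD 0.3 and δ = 0.5. The significant-other rating falls by about 0.49.

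| b | Fall in gap | Share of significant-other change |
|---|---|---|
| 0 | 0.49 | 100% |
| 0.25 | 0.36 | 75% |
| 0.5 | 0.24 | 50% |
| 0.75 | 0.12 | 25% |
| 1 | 0.03 to 0.08 | 5% to 17% (scale floor only) |

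**Effect on the planned comparison.** With equal SDs and zero correlation, the SD of the gap is √2 times that of either rating, so

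spurious d = 0.70 × (1 − b) / √2.

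The chance of two-sided p < 0.05 is taken from a two-sample t test with 27 per arm.

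| b | Spurious d | Chance of p < 0.05 |
|---|---|---|
| 0 | 0.70 / 1.414 = 0.49 | about 43% |
| 0.5 | 0.35 / 1.414 = 0.25 | about 15% |
| 1 | 0 | 5% (the nominal level) |

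**Which b is plausible?** The Background reports that patients rated their forgetting much as controls did, and below what their significant others reported. Self-ratings already that low have little room to fall as memory improves, which suggests b below 1 on average. It does not give a value.

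**The case against.** The strongest reply is that the effect is conditional. Participants can enter the trial because they themselves report PM problems (Eligibility criteria), so some will be aware, with self-ratings that follow their failures; for them the bias is close to nil. The Background statement is a group result from one earlier study. This stands, and it is why the point is worded as can register, in whole or part. A reader might infer that any memory gain automatically counts as an awareness gain; the documents do not support that.

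A reader might also infer a larger effect by letting the two ratings correlate while holding the self-rating still. At a correlation of 0.5 that gives 0.70 / √(2 × 0.5) = 0.70. But it pairs a self-rating that follows the significant other's across people with one that ignores change, and nothing in the document supports that pairing. If the self-rating moves by r times the significant-other change, the spurious effect is 0.70 × √((1 − r)/2), which falls to 0.35 at r = 0.5 (about 24% chance of significance).

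A third tempting inference is that a gap closed only by the significant-other rating means no awareness gain. That is too strong. Someone rated 3 by the significant other and 1 by self at baseline, then 1 and 1 afterwards, may have become accurate. The data leave the question open.

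It is also fair to say that this is one of two secondary awareness measures, that the plan describes no mediation analysis, and that component reporting is often left to a SAP or results paper. Those points limit the consequence. They do not remove the coupling, because the article itself fixes the definition of the outcome and the model applied to it.

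**Conclusion.** The concern holds in conditional form. The awareness gap shares a term with a primary outcome, and the planned model does not show which term moved. A memory gain can therefore narrow the gap with awareness unchanged, unless self-ratings fall one-for-one with failures, which the protocol's own Background makes doubtful.

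The size is illustrative. Under the stated assumptions it runs from about d = 0.49 at most, when self-ratings do not respond, down to near nil when they track fully.

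The AQ is only a partial safeguard. It does not contain the BAPM, but it measures global awareness, is also a self-minus-other score, and includes cognition, so a reader should not infer that it could simply take over the PM-awareness claim. The point limits what the trial may conclude about PM awareness and mechanism. It does not touch the primary outcome.

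**What to change.** - Analyse the participant self-rated BAPM as its own secondary outcome in the same mixed model.
- In every group comparison of the gap, report the self and significant-other changes beside it.
- State in advance that a narrower gap driven only by a fall in the significant-other rating is not, on its own, evidence of improved awareness or of the proposed mechanism. Treat it as indeterminate, not as proof that awareness did not improve.
- Optionally, add a sensitivity model of the self-rating conditional on the concurrent significant-other rating.

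Both ratings are already collected, so no new data or visits are needed. The cost is one extra analysis, a sentence on interpretation and a more cautious awareness claim.

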### Data collection and management

All measures will be completed at the four time points by an assessor who is blind to group allocation. At the preintervention assessment, the assessor will also administer a brief neuropsychological battery consisting of tests of attention (e.g., Digit Span, Trail Making Test A), memory (e.g., Hopkins Verbal Learning Test), and executive function (e.g., Controlled Oral Word Association Test, Trials B, Hayling Sentence Completion Test) in order to provide data on the level of cognitive impairment of the sample. Data on demographic and diagnostic variables (GCS score, duration of PTA, length of hospitalization, and cause of injury) will be retrieved from the participant’s medical records. Significant others will complete the SPRS-2 and BAPM at the clinic if they attend the assessment sessions with the participant with TBI. If they do not attend they will complete the measures at home, with telephone assistance from the assessor if required, and return the questionnaires by post.

Participant retention will be promoted via transport assistance where required and follow-up telephone contact from the project manager. The data management procedure includes cross checking of data using computed and manually scored totals and range checks for data values. Any adverse events will be reported to the research monitoring officer of the Human Ethics Research Committee.

### Sample size

To determine the required sample size, a power calculation was conducted using the primary outcome variable with the most conservative effect size from our previous RCT (i.e., the change score between pre-and post-SPRS-2 scores) [9]. Comparison between the group that received compensatory plus self-awareness training and the group that received compensatory training alone produced an effect size of 0.70 (Cohen’s *d*). Using G*Power [46] and setting the effect size to 0.70, alpha level to 0.05, and power to 0.80 it was calculated that a sample size of *n* = 26 for each group is required. The sample size has been inflated to *n* = 30 per group to allow for an estimated dropout rate of approximately 10% based on dropout rates from another RCT currently being conducted within the same setting [47]. Therefore, it is calculated that a total sample size of *n* = 90 will be required for the study to be adequately powered to detect significant differences between groups.

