In previous research, we developed an 8-week intervention program (consisting of two self-awareness training sessions and six compensatory training sessions) with the aim of rehabilitating the PM of three patients with TBI [8]. The promising findings of this pilot led to a larger-scale randomized controlled trial (RCT) of PM rehabilitation strategies [9], which demonstrated that the six-session compensatory rehabilitation program was more effective than a control intervention in improving PM in people with TBI, as measured by the Cambridge Prospective Memory Test (CAMPROMPT). The control intervention involved a remedial approach of repetitive practice of PM activities over six weekly sessions. The compensatory intervention involved the use of external strategies to both trigger the intention (prospective component) and support retrieval of content salient to the task (retrospective component) over the same time period. Event-based tasks (i.e., taking a cake out of the oven when a timer goes off) are easier than self-initiated or time-based tasks (i.e., remembering to take the cake out of the oven in 40 min) [12]. Therefore, this approach uses compensatory strategies that convert time-based tasks into event-based tasks which provide a cue to initiate performance of the action. Examples are use of an alarm, or linking the task to an event (e.g., taking medication at mealtimes). The significantly greater improvement in PM performance for the compensatory intervention group was attributed to the use of strategies during the PM task. However, these gains did not extend to significantly greater improvements in everyday PM performance or psychosocial function as anticipated. Further research is needed to specifically investigate the generalization of PM compensatory strategies to occupational performance in daily life [29].

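### The 26 per group behind n = 90 reproduces only with an unstated one-sided 5% test, and the adequacy claim is wider than the single contrast calculated

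*Protocol article*

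**What the plan says.** The Sample size section of the protocol article bases the calculation on "the primary outcome variable with the most conservative effect size from our previous RCT (i.e., the change score between pre-and post-SPRS-2 scores"). The contrast is one pair of groups: "Comparison between the group that received compensatory plus self-awareness training and the group that received compensatory training alone". This "produced an effect size of 0.70" (Cohen's d). The remaining settings are "alpha level to 0.05, and power to 0.80". Whether alpha is one- or two-sided is not stated. The result is 26 per group, raised to 30 for about 10% dropout. The section ends by saying that a total of 90 is "required for the study to be adequately powered to detect significant differences between groups".

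Under Study objectives and hypotheses, hypothesis 1 covers more than that contrast. COMP is expected to improve "PM performance and level of psychosocial integration compared to no intervention", and COMP-MST is expected to do better than COMP. The Statistical analysis section plans a linear mixed regression with a three-level group factor on both primary outcomes, and mentions no one-sided test.

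**The concern.** There are two problems in the same paragraph.

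First, the stated inputs do not give 26 per group under the usual two-sided test. A reader who finds alpha 0.05 with no mention of direction, followed by an ordinary mixed-model comparison, will assume two-sided testing and credit the main contrast with 80% power that it does not have.

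Second, the closing sentence speaks of differences between groups in general, while the only input is an effect for COMP-MST versus COMP. The article gives no effect size for COMP versus waitlist. Its nearest evidence is the earlier trial described in the Background, in which compensatory training improved a psychometric test score but "these gains did not extend to significantly greater improvements in everyday PM performance or psychosocial function as anticipated". The comparator there was remedial training, not a waitlist.

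At stake is how a null result is read. A non-significant COMP-MST versus COMP result, or a non-significant COMP versus waitlist result, would be taken as coming from a trial with 80% power and so as fairly strong evidence of no effect. The first has less power than stated, and the second has no stated power at all.

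**Working it through.** **Inputs (Sample size section):** d = 0.70, alpha = 0.05, power = 0.80, 26 per group before dropout, about 10% dropout, 30 per group, three groups.

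**Method.** Two-sample t test with n per group: noncentrality d × √(n/2), degrees of freedom 2n − 2. Power is the probability that the noncentral t exceeds the critical value. This approximates the planned mixed model.

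**1. Reproducing the plan's figure.** The normal approximation is n = 2(z_alpha + z_power)²/d².
- One-sided: 2 × (1.645 + 0.842)²/0.49 = 25.2, rounded up to 26. The exact t calculation gives 25.94, so 26, with power 80.1%.
- Two-sided: 2 × (1.960 + 0.842)²/0.49 = 32.0. The exact t calculation gives 33.02, so 34.

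The stated 26 is therefore the one-sided answer.

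**2. Dropout.** 26/0.9 = 28.9, so 29; the plan uses 30. Expected completers are 30 × 0.9 = 27 per arm.

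**3. Power of the one contrast calculated, at d = 0.70.**

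| n per arm | Noncentrality | Power, one-sided 5% | Power, two-sided 5% |
|---|---|---|---|
| 26 | 2.52 | 80.1% | 69.7% |
| 27 (completers) | 2.57 | 81.4% | 71.4% |
| 30 (all randomised) | 2.71 | 85.0% | 76.0% |
| 34 | 2.89 | 88.7% | 81.2% |

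**4. Effect detectable with 80% power, two-sided.** At 27 per arm, d = 0.78. At 30 per arm, d = 0.74. Both exceed the planning value of 0.70.

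**5. Scope of the claim.**

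| Part of hypothesis 1 | Effect size given in the Sample size section |
|---|---|
| COMP-MST versus COMP, SPRS-2 | 0.70 |
| COMP-MST versus COMP, everyday PM | none given; implied to be no smaller, since SPRS-2 is called the most conservative |
| COMP versus waitlist, SPRS-2 | none |
| COMP versus waitlist, everyday PM | none |

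For scale only: if the COMP versus waitlist effect were 0.3, 0.4 or 0.5 (assumed values, not from the article), two-sided power with 27 per arm would be 19%, 30% or 44%.

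**6. Illustration of joint success.** This assumes that all four parts must be significant, that every effect is 0.70, and that the correlation between outcomes lies between 0 and 0.8. Simulation with 20,000 runs and 27 per arm gives 21% to 33% two-sided and 40% to 51% one-sided. The article sets no such success rule, so these figures are conditional.

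**The case against.** Five points can be made for the plan.

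- **A one-sided test may have been intended.** The hypotheses are directional, and on that basis the single contrast has 81% power with 27 completers. This stands as a possible explanation, but the article does not say so. If it is the intention, it has to be stated and carried into the analysis.
- **More than 27 per arm may be analysed.** The Statistical analysis section imputes the most recent available value, so up to 30 per arm could contribute. This stands, and is why the range runs up to 76%. Even that upper figure is below 80%, and it ignores any dilution from the imputation.
- **The trial was sized on the outcome with the smallest effect.** This is standard practice and largely answers a complaint about the second primary outcome: if its effect is larger, its own test has at least the same power. It does not help COMP versus waitlist, because the choice was made among outcomes while the contrast stayed fixed.
- **The calculated contrast matches the primary aim.** The primary aim is the added value of metacognitive training, and COMP-MST versus COMP isolates it. This is true, and it supports keeping that contrast as the basis. It does not support the wider closing sentence.
- **The mixed model may gain precision.** Baseline adjustment and repeated measures could change power. The article claims no such gain, and d is already on the change score.

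A reader might go further and infer that the plan promises 80% power for the whole of hypothesis 1 and falls far short of it. The article does not support that. It sets 0.80 for one contrast only and contains no rule that all parts must succeed together, and effects other than 0.70 on SPRS-2 are unknown. Nor does the earlier null result show that COMP versus waitlist is underpowered, since its comparator was an active remedial programme.

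**Conclusion.** The point holds in two parts.

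The arithmetic part needs no assumption beyond an ordinary two-sided 5% test of two means. On that basis the stated 80% becomes about 71% with 27 completers per arm, or 76% with all 30. The requirement becomes 34 rather than 26 per arm before dropout, and the detectable effect is 0.74 to 0.78 rather than 0.70. If the sponsor meant a one-sided test, 26 is correct and the defect is that the direction is not stated.

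The scope part is one of wording: the adequacy claim has no input for COMP versus waitlist and does not follow for that contrast. How much power that contrast has cannot be determined from the article. The figures for assumed effects of 0.3 to 0.5 and the joint-success figures are illustrations, not demonstrated shortfalls.

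**What to change.** Revise the Sample size section as follows:

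1. State the sidedness. Either give about 71% to 76% two-sided power for COMP-MST versus COMP on SPRS-2 change at d = 0.70 (27 to 30 per arm), with a detectable effect of 0.78 to 0.74 at 80% power, or say openly that the figure assumes a one-sided 5% test and make the analysis section agree.
2. Limit the adequacy claim to that contrast and outcome.
3. State that no power is claimed for COMP versus waitlist, or for meeting all parts of hypothesis 1 together.
4. Report all primary comparisons with confidence intervals. They can all remain primary; none needs to be demoted.

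Any joint-power figure that is added should be labelled as an illustration under an assumed rule that all parts must succeed, with every effect at 0.70.

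The cost is a less favourable power statement, or an explicit one-sided assumption, and no extra participants. By contrast, holding 80% two-sided power at 10% dropout would need 34/0.9 = 37.8, so 38 per arm and 114 in total; this correction does not require that.
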